## Enrollment Visit

HIV-1 negative persons who meet all of the inclusion criteria and none of the exclusion criteria at screening will be scheduled for an enrollment visit within 45 days of screening. The screening and enrollment visits may be spread over 2-3 visits. Study product must be initiated within 24 hours after the enrollment visit for participants randomized to one of the immediate treatment arms.

The following procedures and evaluations are to be performed at the enrollment visit:

*Epidemiologic/behavioral risk assessment*

Study staff will instruct participants on how to complete a 30 minute audio-computer administered self-interview (ACASI). This interview will collect risk behavior, adherence, and other behavioral data at enrollment and designated intervals throughout the study.

Clinical assessment:

- Enrollment form
- Baseline Medical History Form
- Concomitant Medication Form
- Complete Physical Examination

*Laboratory assessment:*

HIV-1 whole blood rapid EIA.

- Chemistry profile
- Hematology profile
- Urinalysis
- Urine for *Neisseria gonorrhoeae* (GC) and Chlamydia trachomatis (CT) testing
- Blood sample for storage

HIV risk reduction counseling

- Standardized HIV risk-reduction counseling by trained staff including study-specific issues:
  - the nature of the study (safety)
  - the unknown level of protection from the product
  - the possible assignment to placebo
  - the importance of avoiding HIV risk behaviors
  - symptoms that may be associated with acute HIV infection

Upon completion of enrollment assessments the investigator should dispense study products to those participants randomized to an immediate treatment arm based on the number assigned in the allocation sequence.

## Product administration

Each participant will be randomly assigned a unique ID number that corresponds to a pre-labeled, blinded, bottle of study product (TDF or placebo) tablets. At the enrollment visit for the immediate treatment arms and at the 9 month visit for the delayed treatment arms, participants will receive 37 tablets. They must return within 1 month after initial product receipt for a safety visit before receiving further study product. At the 1 month (immediate arm) and 10 month (delayed arm) visits participants will **have any returned pills re-dispensed and will** receive **an additional** 68 tablets. At subsequent quarterly visits, participants will receive 105 tablets.

Participants will be instructed to orally self-administer one tablet daily. The tablet should be swallowed whole. It is important to take the tablets regularly. Each dose should be taken as close as possible to twenty-four hours apart at the same time each day.

The participant will be counseled regarding signs and symptoms of toxicity and the importance of adherence. Two weeks and two months after the enrollment visit for the immediate arms and at 9.5 and 11 months for the delayed arms, participants will receive a phone call from study staff to assess any immediate problems. In addition, participants will be encouraged to call for any adverse experiences possibly related to study product, all serious adverse events, symptoms of acute retroviral infection or concerns regarding product adherence. Participants will be instructed to return unused study medication at each study visit and about the correct use of the MEMS® cap. Participants should not share or dispense study product to any other persons.

Dosage Modification

No modification of dosage will be allowed from this study. If a dose is forgotten, it should be taken as soon as remembered on that same day that it was missed. If a daily dose is missed, the participant should not double the dose the next day.

*Adherence Reminder Sessions*

Face-to-face adherence reminder sessions will take place at the initial product dispensing and each study visit thereafter. This session will include:

- The importance of following study guidelines for adherence to once daily study product
- Instructions about taking study pills including dose timing, storage, and importance of taking pills whole, and what to do in the event of a missed dose.
- Instructions about the purpose, use, and care of the MEMS® cap and bottle
- Notification that there will be a pill count at every study visit
- Reinforcement that study pills may be TDF or placebo
- Importance of calling the clinic if experiencing problems possibly related to study product such as symptoms, lost pills or MEMS® cap.

Subsequent sessions will occur at the follow-up visits. Participants will be asked about any problems they are having taking their study pills or using the MEMS® cap.  There will be brief discussion of reasons for missed doses and simple strategies for enhancing adherence, e.g., linking pill taking to meals or other daily activities.  Participants will have an opportunity to ask questions and key messages from the initial session will be reviewed as needed.

## Dual-energy X-ray Absorptiometry (DEXA) Scans

During the screening process, SFDPH participants will be scheduled for a whole body DEXA scan prior to enrollment. All participants who receive a Z-score of less than or equal to 2.0 standard deviations [SD] below the age appropriate mean on the baseline DEXA scan at the total spine, total hip, or femoral neck will have an evaluation of secondary causes performed as part of the study protocol. This work-up will include a thyroid stimulating hormone, 25-hydroxy vitamin D level, testosterone level, a spot urine calcium/creatinine ratio, and additional testing for other secondary causes suggested by the history and physical. Participants with a spot urine calcium/creatinine ratio of > 0.3 will have a 24-hour urine calcium level performed. In addition, participants over the age of 40 will have a serum parathyroid level checked. Participants with an abnormal work-up or with a Z-score of less than -2.5 will be referred to a primary care provider for further work-up and treatment. All participants with a Z-score of less than -2.5 SD at any of the three sites listed above, or participants who are undergoing treatment for secondary causes of low bone density, will not be eligible for enrollment.

Participants will receive subsequent DEXA scans at 12 and 24 months in the immediate arm, at 9 and 24 months in the delayed arm, and at the time of study discontinuation, if at least 6 months has passed since the previous scan. The 9 month DEXA scan in the delayed arm will be performed before the 9 month visit and before initiating study drug if possible. All other follow-up DEXA scans will be performed +/- 1 month of the target visit if possible. If a subsequent DEXA scan detects a > 5% decrease in bone mineral density from baseline at the either the total hip or total spine sites, a work-up for secondary causes (as described above) will be initiated, study product will be discontinued, and participants will continue to be followed at regularly scheduled visits until completion of study visits.

Participants taken off study drug due to low bone density will continue to be followed for the duration of the study. Participants randomized to the delayed arm will have a DEXA scan performed prior to their 9-month visit if possible, but no later than 14 days after initiation of study drug. All previously enrolled participants whose initial DEXA scan demonstrates a Z-score of less than or equal to -2.0 will be evaluated for secondary causes as described above, and if the work-up is abnormal, will be referred to their primary care provider for treatment. Participants with a baseline Z score of less than -2.5 at the total spine, total hip, or femoral neck will remain off study drug but continue follow-up. Participants whose baseline Z scores at all three locations were greater than or equal to -2.5 will be allowed to restart study drug at the discretion of the investigator.

The radiation exposure associated with DEXA scans is relatively low, and comparable to background radiation. Bone density DEXA scans are associated with exposures of approximately 4 mrem per site, similar to the radiation exposure that would be received in a commercial flight across Canada. Whole body DEXA scans for body fat composition assessment are associated with a dose of approximately 0.04 mrem, which is similar to the background radiation received in the course during the course of one day of normal activities.

## Concomitant Medications

At each study visit information regarding concomitant medications/therapies will be solicited from participants and recorded accurately on study CRFs. As participants will be provided STI testing at the study site, STI results and subsequent treatment must be clearly documented on study CRFs. In addition, concomitant medications administered at the time of a serious adverse event will also be collected. Should participants report treatment with any excluded concomitant medication or experimental agent as specified in Section 5.4, study product will be discontinued while on the disallowed concomitant medication.

### Post-exposure Prophylaxis (PEP)

Antiretrovirals for PEP will not be offered as part of this study, however participants may receive them through outside sources. CDC guidelines recommend a 28-day course of PEP for non-occupational exposures with a known HIV-infected or highly-suspected partner within 72 hours of exposure. If participants select to receive PEP outside of this study, they should inform their PEP provider of study participation and stop study product for the duration of the PEP course. Study staff and PEP providers should follow participant’s clinical course. At the conclusion of PEP, healthy HIV-uninfected participants may resume study product. Participants will be specifically asked about PEP at study visits and data (circumstances, antiretrovirals used, follow-up, and HIV status) will be collected.

## Telephone Calls

Once participants receive study product, either at the enrollment visit (immediate arms) or at their 9 month visit (delayed arms) they will arrange with study staff for a scheduled telephone call at 2 weeks and 2 months following study product initiation to report any potential study-related symptoms or problems. If the symptoms resulted in the participant choosing to discontinue study product or require further clinical assessment, the participant will be requested to return promptly to the study site for evaluation and to return unused study product.

## Follow-up Visits

Participants assigned to the immediate treatment arms will be scheduled for follow-up visits at 1 and 3 months after enrollment and then at months 6, 9, 12, 15, 18, 21, and 24 (Table 1, Appendix 3). Study visits for participants assigned to the immediate treatment arm are to be completed + 7 days based on the enrollment visit date. Participants assigned to the delayed treatment arms will be scheduled for follow-up visits at 1 and 3 months after enrollment and then at months 6, 9, 10, 12, 15, 18, 21, and 24 (Table 2, Appendix 3). Study visits for participants assigned to the delayed treatment arm are to be completed + 7 days based on their enrollment visit until their initial dispensing visit . After the initial dispensing visit (month 9), study visits for participants assigned to the delayed treatment arm will be completed + 7 days based on their month 9 visit date. Regularly scheduled evaluations will be made on all participants whether or not they continue to receive study product.

The following procedures are to be performed at all visits unless otherwise specified:

*Epidemiologic/Behavioral Risk Assessment*

- ACASI (3, 6, 9, 12, 15, 18, 21, and 24 months)

Clinical assessment

- Symptom-directed physical examination
- Administration of Adverse Events/Intercurrent Illness Form
- Concomitant Medication Form

*Laboratory assessment:*

- Hematology profile
- Chemistry profile
- Urinalysis
- Blood sample for storage
- Plasma
- Peripheral Blood Mononuclear Cells (PBMCs) (12 months for immediate treatment arms, 21 months for delayed treatment arms only)
- HIV-1 rapid whole blood EIA (3, 6, 9, 12, 15, 18, 21, and 24 months)
- DEXA scan **(SFDPH only: 12 and 24 months for immediate treatment arms, 9 and 24 months for the delayed treatment arms)**
- STI testing
- RPR (12 and 24 months)
- Urine for GC and CT (6, 12, 18, and 24 months)

Standardized HIV risk reduction counseling as per enrollment visit

During the 24 months of the study, additional HIV testing may be requested at any time by study participants, or may be performed as required by the protocol in the case of an indeterminate result or to help determine the timing of HIV infection more precisely.

After participants complete all scheduled study visits, they will be contacted periodically until final study closeout. The purpose of these interim contacts will be to update contact information and to inform participants of the progress of and timeline for completing the study.

## Evaluation of Suspected Acute HIV Infection

Participants who present with signs and symptoms suggestive of acute HIV infection will be evaluated and the following procedures will be performed:

- Symptom-directed physical examination
- Rapid HIV whole blood antibody test with risk reduction counseling emphasizing the increased potential for transmission of HIV during periods of viremia associated with acute infection.

If HIV rapid test is negative, an HIV-ribonucleic (RNA) polymerase chain reaction (PCR) assay will be performed to detect and quantitate viremia. If RNA PCR is also negative, both HIV RNA PCR and rapid HIV antibody testing may be repeated in 4 weeks or sooner at the investigator’s discretion.

The diagnosis of acute HIV infection will require 2 consecutive viral load quantitations of ≥ 5,000 copies/ml in the setting of a negative HIV EIA antibody tests and negative or indeterminate Western Blot (WB) or immunofluorescent assay (IFA) (54). However, any quantifiable viral load will be repeated for confirmation in addition to serial HIV antibody testing and WB assays.

For all participants presenting with suspected acute HIV infection, study product will be continued unless HIV RNA PCR is quantifiable, HIV antibody is detected, or post-exposure prophylaxis is begun. Otherwise, study product will be held for any quantifiable viral load and permanently discontinued upon confirmation of HIV infection. If HIV infection is detected, the participant will be asked to continue in the study in Part B of the protocol (Section 7).

## Early Study Product Discontinuation Visit

If a participant permanently discontinues study product prior to month 24, he will be asked to return to the study site within 72 hours of stopping study drugs for Early Study Product Discontinuation Visit and to return unused study product. These participants will then be asked to continue attending the scheduled study visits through the month 24 visit.

At the Early Study Product Discontinuation Visit, any evaluations showing abnormal results that there is a reasonable possibility of a causal relationship with the study drug should be repeated weekly (or as often as deemed prudent by the investigator) until the abnormality is resolved, returns to baseline, or is otherwise explained.

The following evaluations are to be completed at the early study drug discontinuation visit:

*Clinical assessment*

- Symptom-directed Physical Examination
- Adverse Events/Intercurrent Illness Form
- Concomitant Medication Form
- Status Change

*Laboratory Assessment*

- Hematology profile
- Chemistry profile
- Urinalysis
- Rapid whole blood HIV-1 EIA testing
- Blood sample for storage

*HIV Risk Reduction Counseling*

## Criteria for Suspension of Study Product

Participants will be discontinued from receiving further study tablets for the following reasons:

- Confirmed HIV-1 infection
- Concurrent illness which, in the investigator’s opinion, may be exacerbated by continued product administration, requires treatment which is contraindicated by the protocol, jeopardizes further compliance or follow-up, and may confound the interpretation of adverse events.
- Unacceptable toxicity, as defined in the toxicity management section of the protocol, or which in the judgment of the investigator, compromises the ability to continue study-specific procedures, or is considered to not be in the participant’s best interest.
- Participant request to discontinue for any reason.
- Any clinical condition or social situation that, in the opinion of the investigator, jeopardizes compliance with study product and may confound the interpretation of clinical adverse events
- Non-compliance with at least two consecutive study visits and a clinical or social situation that in the opinion of the investigator would preclude further compliance with study product
- Non-compliance with at least three consecutive study visits and a clinical or social situation that in the opinion of the investigator and CDC would preclude further compliance with study product

Study investigators must make every attempt to continue follow-up visits for the full 24 months whether or not all study medications have been used. Reasons for premature termination from study medication or follow-up visits will be reported on the specific CRF.

## Early Study Termination Visit

If the participant terminates study participation prior to month 24, he will be asked to return to the study site for an Early Study Termination Visit and to return any unused study product. At this visit, any evaluations showing abnormal results that there is a reasonable possibility of a causal relationship with the study drug, should be repeated weekly (or as often as deemed prudent by the investigator) until the abnormality is resolved, returns to baseline, or is otherwise explained.

The following evaluations are to be completed at the early study termination visit:

*Epidemiologic/Behavioral Risk Assessment*

- ACASI

*Clinical assessment*

- Symptom-directed Physical Examination
- Adverse event/Intercurrent Illness Form
- Concomitant Medication Form
- Status Change

*Laboratory assessment*

- HIV-1 whole blood rapid test
- Hematology profile
- Chemistry profile
- Urinalysis
- STI testing
  - RPR
  - Urine for GC and CT
- DEXA scan (for SFDPH subset if > 6 months since last scan)
- Blood sample for storage

## Criteria for Early Study Termination

Participants may be discontinued from the study for the following reasons:

- Participant request to discontinue for any reason.
- Participant non-compliance with study visits or procedures.
- Any clinical condition or social situation that, in the opinion of the investigator, would make the participant unable to comply with the protocol requirements.

Reasons for premature termination from study product or follow-up visits will be reported on the specific CRF.

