# STATISTICAL CONSIDERATIONS

## Study Design and Analysis Plan Overview

This is a phase II randomized double-blinded placebo-controlled trial to assess the clinical and behavioral safety of daily oral use of TDF among MSM. Four hundred MSM at risk of HIV-1 infection will be recruited from two sites, randomized 1:1:1:1 to one of four treatment arms, and followed for 24 months. Two treatment arms will receive study product (TDF or placebo) for the entire 24 months (the immediate treatment arms) and the other two treatment arms will receive no study product for the initial 9 months and then receive either TDF or placebo for the remaining 15 months. The data analysis will compare clinical and behavioral safety data between the study arms. The analysis will employ the intent-to-treat principle whereby all data from enrolled participants will be analyzed according to the initial randomization assignment regardless of how many doses they received.

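### Section 6.13 lets follow-up be ended for missed visits or procedures with no threshold, a looser test than 6.11 sets for stopping tablets and in tension with following all men to month 24

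*Protocol*

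**What the plan says.** Protocol section 6.13 opens with "Participants may be discontinued from the study for the following reasons" and gives three grounds. The second is "Participant non-compliance with study visits or procedures". It has no minimum count of missed visits, no list of procedures and no call for sponsor agreement. The reason is recorded on a CRF.

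Four other sections bear on the same man:

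- 6.8, Follow-up Visits: "Regularly scheduled evaluations will be made on all participants whether or not they continue to receive study product".
- 6.10, on men who stop product early: "These participants will then be asked to continue attending the scheduled study visits through the month 24 visit".
- 6.11, after its list of reasons for stopping product: "Study investigators must make every attempt to continue follow-up visits for the full 24 months whether or not all study medications have been used".
- 10.1: "all data from enrolled participants will be analyzed according to the initial randomization assignment regardless of how many doses they received".

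Section 6.11 also sets its own test for stopping product over missed visits. The lower level is two consecutive visits plus a clinical or social situation, in the investigator's opinion. The higher level reads "Non-compliance with at least three consecutive study visits and a clinical or social situation that in the opinion of the investigator and CDC" and goes on to require that this situation would preclude further compliance with product.

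**The concern.** Ending follow-up costs intent-to-treat data; stopping tablets does not. Yet the step that costs data has the lower bar.

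This matters most for the main behavioral safety analysis (10.6), which compares the immediate and delayed arms over the first nine months. That assignment is open: under 5.2 the envelope tells site staff which it is, and delayed men have no pills until month 9. (TDF versus placebo is blinded, so the point is weaker there.) Men who miss visits may differ in risk behavior from those who attend. If some of them are withdrawn who could have come back, and this happens more in one open arm than the other, the comparison is no longer between the groups as randomised. The drop-out checks in 10.5 and 10.6 compare those who leave with those who stay, overall or within site by study group. They cannot recover behavior that was never reported.

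**Working it through.** **1. The two rules side by side.**

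| Action | Missed-visit threshold | Further condition | Decision-maker named |
|---|---|---|---|
| Stop product (6.11) | at least 2 consecutive | clinical or social situation | investigator |
| Stop product (6.11) | at least 3 consecutive | clinical or social situation | investigator and CDC |
| End study follow-up (6.13) | none | none | none |

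Section 6.13 has a separate ground for men whom a clinical or social situation makes unable to comply. What the non-compliance ground adds is therefore mainly the withdrawal of men who could still return.

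**2. The plan's own figure for the comparison at stake.** Section 10.6 claims more than 80% power for a 12-point difference when the delayed-group probability is at least 28%. Inputs: 200 per group (10.3); two-sided alpha 0.05 (stated in 10.3 for the SAE table, assumed here); three follow-up visits at months 3, 6 and 9; within-man correlation 0.5 (stated in 10.7 for adherence, assumed here).

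- Effective n per group = 200 × 3 / (1 + 2 × 0.5) = 300.
- Power for 28% v 40%, mean 34%: z = [0.12 − 1.96 × √(2 × 0.34 × 0.66 / 300)] / √[(0.28 × 0.72 + 0.40 × 0.60) / 300] = (0.12 − 0.0758) / 0.0384 = 1.15, so power = 0.875.

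At correlation 0.7 power is 0.810; on a single visit it is 0.718. The claim is reproduced, and it is not disputed.

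**3. Illustration A: more removal in the delayed arms, no true difference.** Assumed: true prevalence 30% in both arms; removed men have prevalence q; 5% of immediate men are removed by month 9. Prevalence among those remaining = (0.30 − r × q) / (1 − r), where r is the fraction removed.

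| r | q = 50% | q = 60% |
|---|---|---|
| 5% (immediate) | 0.275/0.95 = 28.9% | 0.270/0.95 = 28.4% |
| 10% (delayed) | 0.250/0.90 = 27.8% | 0.240/0.90 = 26.7% |
| 15% (delayed) | 0.225/0.85 = 26.5% | 0.210/0.85 = 24.7% |
| 20% (delayed) | 0.200/0.80 = 25.0% | 0.180/0.80 = 22.5% |

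Immediate minus delayed, from unrounded values: 1.2, 2.5 and 3.9 points at q = 50%; 1.8, 3.7 and 5.9 points at q = 60%. This is a false excess of risk in the immediate arm.

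**4. Illustration B: removal in the immediate arm only.** Let 10% be removed, with 1.5 to 2 times the arm's average risk.

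- True 40% v 28%: (0.40 − 0.10 × 0.60)/0.90 = 37.8% and (0.40 − 0.10 × 0.80)/0.90 = 35.6%. The 12-point difference shows as 9.8 or 7.6 points, and power (effective n 270 v 300) falls to 0.70 or 0.49.
- No true difference, 28% in both: (0.28 − 0.10 × 0.42)/0.90 = 26.4% and (0.28 − 0.10 × 0.56)/0.90 = 24.9%, a false difference of −1.6 to −3.1 points, with a rejection rate of 0.07 to 0.13 in place of 0.05.
- Removal unrelated to behavior: no bias, and power falls only from 0.875 to 0.858.

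A and B have opposite signs, so the direction is not fixed.

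**5. What both illustrations leave out.** They drop a removed man completely. ACASI is scheduled at enrollment and months 3, 6 and 9, so answers given before removal stay in the longitudinal model. Take the 5% v 20% case at q = 50%, and suppose each removed man had already given one of his three follow-up reports, with visits weighted equally. The shares of reports lost are then 0.05 × 2/3 = 0.033 and 0.20 × 2/3 = 0.133. Remaining prevalences are (0.30 − 0.0167)/0.967 = 29.3% and (0.30 − 0.0667)/0.867 = 26.9%, a difference of 2.4 points instead of 3.9. An ACASI at the termination visit (6.12) would reduce it further. This uses the 10.1 principle. Section 10.4 limits the ITT population to men with at least one dose, which would exclude a delayed man withdrawn before month 9; that is a separate inconsistency, and I do not rely on it.

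**The case against.** The strongest reply is that the sections can be read together. The sentences in 6.8, 6.10 and 6.11 mainly say that stopping product does not end follow-up. The duty in 6.11 is one of best effort, and its next sentence foresees premature termination of follow-up visits. Section 6.13 is permissive. So a site would first try to keep the man and end his participation only when that fails. This stands as far as it goes: the text is in tension, not in flat contradiction. But nothing in 6.13 makes those attempts a condition, so a site that follows 6.13 alone complies with it while giving up data it could have had.

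The reply on size also stands. A man who misses visits is already not supplying data, so this ground costs only what he would have supplied later. The 20% removal case puts on one ground, by month 9, the top of the 10-20% loss from all causes that 10.3 expects over the whole study. CRF reasons and drop-out comparisons show that the plan recognises the problem.

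A reader might infer four stronger points that the documents do not support:

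- That 10.3 predicts unequal withdrawal because it mentions participation in the delayed arms. That remark concerns the choice of allocation and lead-in, and the following paragraph speaks of recruitment.
- That a terminated man can never return data. No section says so.
- That the ground is expressly left to the site. It names no decision-maker; only the third ground cites the investigator's opinion.
- That 1 to 6 points is the expected bias.

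**Conclusion.** The point holds as a drafting and design weakness that should be corrected. Section 6.13 allows follow-up to be ended for non-compliance on a looser test than 6.11 applies to tablets, and this works against 6.8, 6.11 and 10.1 in the one main comparison where the assignment is open.

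Bias is possible but not shown. It needs withdrawals that are related to risk behavior and that differ between the arms, and the protocol gives no rate for either. The range of 1.2 to 5.9 points, against the 12-point design difference, is an upper illustration. It rests on assumed removal of 5% v 10-20%, an assumed prevalence of 50-60% in removed men against 30% overall, and no use of their ACASI data from before removal or from the termination visit. The sign could be either way.

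**What to change.** In 6.13, remove non-compliance with visits or procedures as a ground for ending Part A follow-up. Non-compliance would then bear on study product only, under the 6.11 criteria, which this change leaves as they are. The other two grounds in 6.13 (participant request and inability to comply) stay.

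Add a sentence: men who miss visits or procedures remain enrolled and eligible for all later visits and ACASI unless they withdraw or cannot continue, and are classed as lost to follow-up only if not reached by the month 24 visit window.

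The cost is one deleted bullet, one added sentence and some extra effort to contact poor attenders, which 6.11 already asks for. A man's right to withdraw is untouched.
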